### Overview of the MFG intervention

MFG-SCI uses a structured problem-solving and skills training approach to provide individuals with SCI and their caregivers with tools and information to improve coping and help family members to reconnect through positive behavioral exchanges. MFG educators are health professionals with experience in management of SCI, such as physical therapists, occupational therapists, and psychologists. MFG-SCI consists of three sequential phases: (1) a “Joining” in which MFG educators meet with each individual dyad for 2–3 sessions to allow participants to become acquainted with the educators, evaluate ongoing problems, and define treatment goals; (2) a 2-session Educational Workshop which provides information about SCI to all persons with SCI and their caregivers; (3) bi-monthly multifamily group meetings for 6 months (12 sessions) which provide a structured format for building problem-solving and communication skills while receiving social support. These 12 sessions will be divided into three 4-session phases: SCI management and self-care, coping, living with SCI, and staying healthy after SCI. Through instilling a systematic approach to solving everyday problems related to SCI challenges, MFG aims to reduce emotional distress and improve skills and supports through enlisting the caregiver’s practical and emotional support for the person with SCI.

The educator joining with each couple also leads the group. Although the structure and contents of the MFG Joining and Workshop are provided in the relevant sections of the treatment, the focus here is on describing the structure of the MFG problem-solving sessions. The group sessions consist of 3 components: (1) A brief (15-min) period for socialization, unwinding and “small talk”; (2) after 15 min, the educator starts the “Go Round” in which each couple relates briefly how the past 2 weeks have gone for them, including follow-up on homework or problem-solving recommendations. The educators take this opportunity to amend plans which have not been successful, offering a modification of the original or an alternative solution. Based on the Go Round, a problem or goal is selected for the current week’s group exercise. Thirty-five minutes are allotted to the Go Round, including problem selection. (3) The educators then lead the group in formal problem solving for approximately 35 min, using a six step process based on brainstorming methods from organizational and business practices.Step 1. Define the problem or goal (MFG members & educators);Step 2. List all possible solutions (MFG members);Step 3. Discuss advantages and disadvantages of each in turn (MFG members & educators);Step 4. Choose the solution that best fits the situation (MFG members);Step 5. Plan how to carry out this solution (Educators);Step 6. Review implementation (Educators).

The proceedings will be recorded on a whiteboard, to facilitate group participation and record the results. After the problem-solving exercise, 5 min are reserved for a wind-down before ending. This treatment approach differs from those that deliver information or develop skills in a planned sequence. Instead, problems are addressed as they occur in the course of participants’ daily lives. Solutions to emergent or continuing problems are generated by the group and/or by the educators, drawing on their knowledge of general problem-solving and compensatory strategies keyed to specific problems (e.g. pain, bladder management, pressure sores, needed home modifications), using the educators as consultants. The solutions are then implemented as homework, and reviewed during the next session. This approach has the advantage of ecological validity, a key aspect of rehabilitation interventions often lacking in more formulaic interventions [37].

### Comparison condition: SCIEC

The SCIEC condition is a 16-session, highly structured educational intervention that provides information on how SCI affects the body; methods for maximizing function, coping, and living with SCI; and staying healthy with SCI. It also includes general guidelines for improving health behavior. The content for these areas is based on a highly recognized self-care guide for persons with SCI [25]. Areas of focus in MFG-SCI, such as coping with SCI problems or dyad relationship and family readjustment issues, are explicitly not addressed in SCIEC. Each SCIEC session follows the same structure, beginning with a presentation of the objectives for the current session and a brief review of material from the previous session before introducing the session’s topic and presenting information on one or two key problem areas. In order to limit opportunities for group interaction and development of group cohesion, SCIEC utilizes a traditional didactic model with information delivered by the educator in a classroom or lecture setting (where all chairs face the educator). In addition, the information provided is general and broad-based, rather than focused on individual participants’ concerns. To avoid overlap with MFG problem-solving skills training, individual health problems will not be discussed. Instead, participants will be referred to their provider or supplied with a referral as needed. By contrast, MFG-SCI is designed to foster group support by delivering skills training in a round-table setting where all group members are encouraged to join in problem-solving exercises. Furthermore, the MFG educators’ approach is collaborative, and the materials are drawn from the everyday problems brought in by group members. Consistent with an educational model, handouts summarizing session material are provided in SCIEC; whereas in MFG-SCI homework is assigned as an integral feature of skills training and rehearsal and repetition are critical components of skills acquisition.

Table 2 shows the key structural-conceptual differences between conditions, while Table 3 summarizes the overall structure of the two conditions, including the different phases, components, and basic material delivered in each intervention. Table 3 also demonstrates that the two conditions are identical in number of sessions, but differ in treatment strategies (skills training vs. general education without reference to or problem-solving about participants’ individual health concerns/behavior).

**Table 2 Tab2:** Comparison of MFG-SCI and control treatment (SCIEC)

Treatment Component	MFG-SCI	SCIEC
Therapeutic Strategy	Skills training, problem solving, support	Information only
Contents	SCI effects on the body, maximizing function, coping, living and staying healthy with SCI	SCI effects on the body, maximizing function, coping, living and staying healthy with SCI
Target Group	Persons with SCI and caregivers	All persons with SCI and caregivers
Use of Group Dynamics/ Cohesion	*Social support promoted*: Entire group participates in problem-solving for each dyad and gives support and encouragement	*Social support minimized:* Individual health issues not discussed, education is general, group interaction minimized
Therapeutic Stance	Educator stance is collaborative	Educator stance is didactic
Room Set-up	Round table	Lecture style (all chairs face forward)
Source of Material	Drawn from everyday problems brought in by group members	Supplied by educator
Homework	Assigned and reviewed at the start of the following session	Handouts but not homework provided

**Table 3 Tab3:** Comparison of MFG-SCI and control treatment (SCIEC)

Treatment Component	MFG-SCI	# sessions	SCIEC	# sessions
Joining	*Dyad-tailored Education*: ^a^ SWOT analysis, SCI problems identified and corrected.	2(3) ^b^	*Standard Dyad Intake:* History of person with SCI and caregiver focusing on current health, skin care, bladder management, bowel management. No skills training, interventions, or formulation of management problems and needed adjustments.	2(3) ^b^
	*Formulation* of management problems and coping. Recommend one or more strategies and adjustments (individual and dyad).			
Group Introductory Sessions	*Educational Workshop:* ASIA classification, clinical syndromes, rehab therapy, medications, health lifestyle, the family and adjustment, family guidelines. Structure and function of multifamily group, how it can help.	2	*SCIEC Education Introduction:* Structure and rationale for intervention. Rules of conduct. Overview of topics to be covered.	1
Ongoing Group Sessions	*Problem-solving & Skills Training Sessions:* Problem-solving designed to address specific problems associated with SCI. Compensatory strategies for SCI problems, planning ahead.	12	*SCIEC Education:* General information provided to promote healthy living in areas relevant for persons with SCI and caregivers (bladder/bowel management, nutrition, use of alcohol, drugs, safe exercise).	13
			Personal health concerns not discussed; however, discuss referral to provider.	
Total		16		16

^a^In addition to basic intake

^b^The default is 2 sessions, an optional 3^rd^ session may be used to maintain contact with group members recruited early, or where the dyads are uncertain about continued participation

### General analytic approach

Preliminary analyses will include inspection of descriptive statistics and features of the data to determine whether data transformations for non-normal data are necessary. We will initially test whether baseline characteristics of the study population (e.g., age, sex, race, neurological level, extent of lesion) and other variables known to be related to the primary outcomes are comparable between the two treatment groups using independent t-tests or Wilcoxon rank-sum tests for continuous variables, and chi-square or Fisher’s exact tests for categorical variables. Groups will be considered imbalanced on variables that differ at *p* < .10, and all such imbalanced baseline prognostic factors will be included in primary analyses as covariates. We intend to measure the primary and secondary outcomes described in Table 1 at three time points for each participant (SCI patient and caregiver). Because repeated measurements on individual subjects tend to be correlated and, in some cases, the number and intervals of time between observations may vary among subjects, we will analyze each outcome measure with a general linear mixed model (GLMM) for longitudinal (repeated measures) data by modeling for 3 independent variables: Group (MFG-SCI vs. SCIEC), Time Since Inpatient Treatment (0–18 months vs. 19–36 months post-treatment), and Time of Assessment (pre-treatment, post-treatment, and 6-month follow-up) with covariates represented in the analyses as necessary, and individual subject variables will be simultaneously modeled as random effects. GLMM will account for dependence in repeated measures and accommodate correlated errors, unequal correlations among time points, unbalanced data resulting from missing data points, and unequal intervals between testing occasions. All principal analyses will be conducted based on the intention-to-treat principle in which any participant randomized to a treatment arm remains in it regardless of adherence to or completion of treatment. We will measure level of participation and conduct a sensitivity analysis that assesses the stability of the conclusions from the intention-to-treat analysis against an available-case analysis that considers only data from fully-adherent participants in a General Linear Model (GLM) repeated measures analysis of variance (RMANOVA). With multiple time points and variables representing outcomes at both the individual and caregiver levels, the planned analyses involve multiple comparisons, which increases likelihood that any single outcome will be found to be statistically significant based on chance alone. In order to minimize this risk, we have carefully selected a limited number of outcomes and clearly designated primary and secondary outcomes. Accordingly, we will also employ a more stringent observed type I error criterion (*p* = .01) than the typical .05 criterion in order to buffer against potential inflation of Type I errors due to multiple tests being performed in both the GLMM and RMANOVA.

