## Methods and design

We will randomize 32 outpatients with SCI and their caregivers to a 9 month MFG intervention (MFG-SCI, *n* = 16 pairs) or to an SCI education control condition (SCIEC, *n* = 16 pairs) of the same duration. Over time, each condition will have 4 to 5 cohorts of 3 to 5 couple pairs. Participants will receive the different treatments at a single medical rehabilitation hospital. All participants will provide written informed consent prior to participation. The SCIEC condition will be based on the 4th Edition of the book titled: *Yes, you can: A guide to self-care for persons with spinal cord injury* [25]. The content will be taken from four sections of the book and will be covered in 16 bi-monthly sessions: 1. How SCI affects your body; 2. Maximizing your function; 3. Coping and Living with SCI; and 4. Staying healthy with SCI. The study will employ a two-arm randomized intervention-control design with repeated measures of outcomes across time. Depending on characteristics of individuals with SCI who consent to participate, we will stratify participants on time since injury (≤18 months post discharge vs. 19–36 months) and location/severity of the SCI (American Spinal Injury Association [ASIA] Classification system) and randomize to the two conditions, rigorously assessing outcomes of those with SCI and their caregivers. The SCIEC intervention will provide SCI management information in a didactic format, but it will not include the group problem-solving or structured social support afforded by MFG over the same 9-month period. Each of the clinicians will be provided a manual for didactic components of the intervention; in addition, they will receive bi-weekly supervision by the PI. For all participants, we will continue to measure outcomes after completion of the 9-month intervention period in order to assess durability of outcomes.

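### Covariates for the primary analyses are chosen by baseline significance tests at p < .10, which makes the model data-dependent and would almost never admit the ASIA factor if it is used to stratify

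*Protocol article*

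**What the plan says.** General analytic approach sets out a screening step before the main model. The arms are compared on "baseline characteristics of the study population (e.g., age, sex, race, neurological level, extent of lesion" and on other variables known to relate to the primary outcomes. The tests are "independent t-tests or Wilcoxon rank-sum tests for continuous variables, and chi-square or Fisher’s exact tests for categorical variables". The threshold for calling the arms imbalanced on a variable is p < .10. The consequence is stated without exception: "all such imbalanced baseline prognostic factors will be included in primary analyses as covariates".

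The mixed model is then specified "by modeling for 3 independent variables: Group (MFG-SCI vs. SCIEC), Time Since Inpatient Treatment" and Time of Assessment, "with covariates represented in the analyses as necessary". Pre-treatment is one of the three levels of Time of Assessment.

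Two other places bear on this:

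- Methods and design: "Depending on characteristics of individuals with SCI who consent to participate, we will stratify participants on time since injury" (up to 18 months against 19 to 36 months after discharge) and "location/severity of the SCI (American Spinal Injury Association [ASIA] Classification system").
- Table 1: a footnote marks CES-D-10, for patient and caregiver, as a covariate in the analyses.

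**The concern.** In a randomised trial, a baseline difference between arms arises by chance, so testing it answers a question whose answer is already known. What makes a covariate worth including is its relation to the outcome, and the between-arm p-value carries no information on that. The rule can admit a weak predictor that happens to differ and leave out a strong one that happens to be balanced. The form of the primary model is then settled only after the data are seen.

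The rule also works against the design. ASIA location/severity is considered important enough to stratify on, but in the analysis its components (neurological level, extent of lesion) appear only on the screened list. Stratification balances the factor, and balance is what keeps it out of the model. An analysis that ignores a prognostic stratification factor leaves that factor's variance in the error term, so the standard error is too large for the design. With 32 dyads and a .01 criterion, there is little precision to give away.

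**Working it through.** **The plan's own figure.** The article gives no figure for the screening rule. Its nearest figure is the power for the between-group effect, which uses no covariates: effect size .6, two-sided alpha .01, 16 per arm, three measures, correlation .2, power 97%. With lambda = f² × N / [(1 + 2 × rho)/3] = .36 × 32 / (1.4/3) = 24.7 on 1 and 30 df, power is 98.3% if .6 is read as Cohen's f. Read as a standardised difference d, it is 41%. The metric is not stated. That is a separate matter, but it affects how much power is at stake here.

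**How large a difference the rule needs.**

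- Continuous factor, 16 against 16: t(.95; 30 df) × √(2/16) = 1.697 × 0.354 = 0.60 SD. A true imbalance of 0.5 SD would be flagged only 40% of the time.
- Binary factor: 10/6 against 6/10 gives p = .29 by Fisher's test (.157 by chi-square) and is dropped. 11/5 against 5/11 gives p = .076 by Fisher's test and enters.

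**Chance entry.** The article names five example variables. With five independent tests at exactly .10: 1 − .9⁵ = .41. Fisher's test is discrete and admitted an unstratified 50/50 factor in only about 5% of simulated trials. If four of the five factors behave like that, 1 − .9 × .95⁴ = .27. The list is open-ended, and either figure rises with its length.

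**Cost for the Group main effect.** The simulation uses 32 dyads, one 50/50 binary factor, alpha .01, Fisher screening at .10 and 10,000 replicates. The outcome is the three-measure mean with a true difference of 0.6 / √(1.4/3) = 0.878 SD (0.6 SD at each measure). R² is the share of that mean's variance explained by the factor. Stratified randomisation uses permuted blocks of 4 within strata. The factor split, the blocks and R² are assumptions and do not come from the article.

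| Randomisation | R² | Factor selected | Type I error: rule / always included | Power: rule / always included |
|---|---|---|---|---|
| Stratified on factor | .1 | 0 of 10,000 | .009 / .012 | 40% / 45% |
| Stratified on factor | .3 | 0 of 10,000 | .002 / .008 | 39% / 59% |
| Not stratified | .1 | about 5% | .010 / .010 | 42% / 45% |
| Not stratified | .3 | about 5% | .007 / .009 | 41% / 57% |

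The Monte Carlo standard error of a type I rate near .01 is √(.01 × .99 / 10,000) = .001.

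**Which R² is credible.** With a correlation of .2 between measures, a covariate whose effect is constant over time can explain at most 20% of one measure's variance (assuming non-negative residual correlation). For the mean of three measures the ceiling is .2 / (1.4/3) = .43. An R² of .3 is allowed and .5 is not.

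**Group-by-Time.** A covariate effect that is constant over time cancels from the contrast of post-treatment mean minus pre-treatment. With correlation .2, R² = .2, 16 per arm and a post-treatment effect of 1.0 SD, power was 45% without the covariate and 43% with it.

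**The case against.** Much can be said for the plan, and part of it stands.

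- **The rule does not govern every covariate.** A reader might infer that time since discharge is the only fixed adjustment. Table 1 contradicts this, since CES-D-10 is named in advance. The screening sentence also speaks of prognostic factors, so it is not a licence to enter any variable that differs.
- **ASIA is neither excluded nor certain to be a stratifier.** Its components are on the screened list, covariates may enter as necessary, and the stratification is conditional. If ASIA is not used to stratify, the argument about a standard error wrong for the design falls away. The loss of precision and the data-dependence remain.
- **There is no inflation of false positives.** A reader might infer that choosing covariates after looking at the data makes the test too liberal. The simulated error rates under the rule are at or below .01. Nothing in the article suggests that the screening would be repeated with other variable lists.
- **Very large power losses are not supported.** At R² = .5 the same simulation gives 36% against 77%, but that R² exceeds the ceiling of .43 implied by the plan's own correlation. The simulation is also a single-outcome linear model, and its losses do not carry over to Group-by-Time.
- **Power may be near its ceiling.** If the article's effect size is Cohen's f, its stated power of 97% leaves at most 3 points to gain, 5 at 28 dyads (95%), and 13 at 28 dyads with effect size .5 (87%).

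A statistical analysis plan could add detail, but it could not fix the covariates without contradicting the rule as stated.

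**Conclusion.** The point holds in limited form. The article states an affirmative rule that lets chance baseline differences decide part of the primary model. It also treats the two planned stratification factors unequally: time since discharge is always modelled, while ASIA, if used, would in practice be left out.

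The harm is lost precision and a conservative test of the Group main effect, which the article tests (Tests of specific study hypotheses) and powers (Power calculations). Under stratification the loss is about 5 points of power at R² = .1 and 20 at R² = .3. Without it, the loss is about 3 and 17 points. These figures rest on an assumed covariate strength, a 50/50 factor, a true difference of 0.6 SD at every measure and complete data. They are illustrations, not estimates for this trial. Group-by-Time is little affected. The change is worth making because it is cheap and settles the model before outcomes are seen.

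**What to change.** Delete the p < .10 rule and present baseline comparisons as description only. In its place, name the covariates:

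- CES-D-10, as Table 1 already states, except in the model where it is itself the outcome (Table 1 also marks the caregiver CES-D-10 as primary);
- time since discharge, as already modelled;
- the ASIA factor, in the form actually used for stratification. Reducing it to complete against incomplete would drop location and would not be the factor as stratified.

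Do not add the baseline value of the outcome as a covariate while pre-treatment remains a level of the response. The repeated-measures model already uses that value, and entering it again would put it on both sides of the equation.

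The cost is two sentences and 1 to 2 degrees of freedom, or a few more if ASIA is stratified in several levels.

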### Dyad functioning

The Family Crisis Oriented Personal Evaluation Scales (F-COPES) [35] assesses family-level coping including use of social/spiritual support, reframing negative events, and mobilizing the family to acquire/accept help. The F-COPES has been widely used with internal consistency reliability ranging from .82 to .89 [36]. The F-COPES will allow us evaluate, on an exploratory basis, whether improved dyad functioning is mediated by improved coping and will be administered to both dyad members.

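### Both treatments are delivered in cohorts of 3 to 5 dyads, but the model and the power calculation treat dyads as independent; if outcomes correlate within cohorts, the .01 level is exceeded

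*Protocol article*

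**What the plan says.** **Delivery.** The Methods and design section states that "each condition will have 4 to 5 cohorts of 3 to 5 couple pairs", with 16 dyads per arm.

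**Group process.** For MFG, Table 2 says "Entire group participates in problem-solving for each dyad and gives support and encouragement", and the intervention overview adds "The educator joining with each couple also leads the group". The control condition is also taught in groups, but deliberately with little interaction: "In order to limit opportunities for group interaction and development of group cohesion, SCIEC utilizes a traditional didactic model".

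**Model.** The General analytic approach section analyses each outcome with a general linear mixed model "by modeling for 3 independent variables: Group (MFG-SCI vs. SCIEC), Time Since Inpatient Treatment" and time of assessment, with covariates as needed. On random effects it says "individual subject variables will be simultaneously modeled as random effects". On dependence it says "GLMM will account for dependence in repeated measures and accommodate correlated errors, unequal correlations among time points". It names no term for cohort or educator.

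**Power.** The Power calculations section gives 97 % at 16 dyads per arm (effect size .6, two-sided .01, correlation among repeated measures 0.2). It gives 95 % at 14 per arm, and 87 % at 14 per arm with effect size .5. It mentions no ICC and no design effect.

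**The concern.** Dyads that meet for months in the same small group, work on each other's problems and share a leader are unlikely to have fully independent outcomes. This applies most to MFG, where the group is the means by which treatment is meant to work. Part of the outcome variation may then lie between cohorts, and there are only 8 to 10 cohorts in the whole trial.

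A model with subject-level random effects credits all of that variation to individuals. The standard error of the arm comparison is then too small and its degrees of freedom too many, and both errors favour a finding of superiority. The .01 criterion is the plan's numerical protection against multiple testing, so any erosion of it bears on every primary and secondary outcome.

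**Working it through.** **1. Inputs**
- From the article: 16 dyads per arm; 4 to 5 cohorts per arm; cohort size 3 to 5; two-sided alpha .01; effect size .6 (.5 as the conservative case); correlation 0.2; three measurements.
- Assumed: ICC from 0 to .20. This is the ICC of the dyad-level summary being tested, such as change or post-treatment mean.

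**2. The plan's own power figure.** For the between-group effect in a repeated-measures ANOVA, the variance factor is (1 + (3 − 1) × 0.2)/3 = 0.4667. The noncentrality is N × f² / 0.4667, on 1 and N − 2 df.

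| Case | Noncentrality | Computed | Stated |
|---|---|---|---|
| N = 32, f = .6 | 24.69 | 98.3 % | 97 % |
| N = 28, f = .6 | 21.60 | 96.1 % | 95 % |
| N = 28, f = .5 | 15.00 | 85.2 % | 87 % |

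All three agree within 2 points when the effect size is read as Cohen's f. Read as a standardized mean difference they come to 41.0 %, 34.5 % and 22.3 %, which does not reproduce. No cohort term is needed to reach the stated figures, which confirms that dyads were taken as independent.

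**3. Understatement of the standard error.** Design effect = 1 + (m − 1) × ICC, and the standard error is too small by its square root. With m = 4 and both arms clustered:
- ICC .01: 1.03, factor 1.015
- ICC .05: 1.15, factor 1.07
- ICC .10: 1.30, factor 1.14
- ICC .20: 1.60, factor 1.26

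**4. True type I error at nominal .01.** Simulated trials (400,000 per setting) had one summary per dyad and were tested by a two-sample test that ignores cohort. Each cell gives clustering in MFG only, then in both arms.

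| ICC | 4 cohorts of 4 | 5 cohorts (4,3,3,3,3) | 4 cohorts (5,5,3,3) |
|---|---|---|---|
| .01 | .010 / .011 | .011 / .011 | .011 / .011 |
| .05 | .013 / .016 | .012 / .015 | .013 / .017 |
| .10 | .016 / .024 | .015 / .020 | .017 / .025 |
| .20 | .024 / .042 | .020 / .033 | .025 / .046 |

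At ICC 0 the test holds its level.

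**5. Power with a cohort term.** The noncentrality of 24.69 is divided by the design effect, and df = 2 × (cohorts per arm − 1). That gives 6 df with m = 4, or 8 df with m = 16/5 = 3.2. The effect size is f = .6.

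| ICC | 4 cohorts per arm, 6 df | 5 cohorts per arm, 8 df |
|---|---|---|
| 0 | 84 % | 91 % |
| .01 | 82 % | 90 % |
| .05 | 77 % | 87 % |
| .10 | 71 % | 83 % |
| .20 | 61 % | 76 % |

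Most of the loss comes from the degrees of freedom. At ICC .05 with m = 4, the design effect alone (30 df kept) leaves 96 %.

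**6. Can the cohort variance be estimated?** For four cohorts of 4, the ANOVA estimate is zero or negative when F falls below 1, where F is distributed as (1 + 4 × ICC/(1 − ICC)) times a central F. Within one arm (3 and 12 df) the probability is about 50 % at ICC .05 and 43 % at .10. Pooled over arms (6 and 24 df) it is about 44 % and 34 %.

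**The case against.** **The size is unknown.** A reader might infer that the standard errors are certainly too small and that the .01 level certainly fails. The documents do not support that. They give no ICC, the test is exact at ICC 0, and at .01 the excess is negligible. The MFG mechanism makes a positive correlation likely but does not size it. This objection stands, and the point is conditional for that reason.

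**The both-arms figures may be too high.** The control condition is built to suppress interaction, so equal clustering in both arms is one extreme and clustering in MFG only is the other. This stands; hence the ranges. Likewise, the article says that the educator who joins with a couple leads its group for MFG only, so a shared educator in the control arm should not be assumed.

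**Power might seem far worse.** Reading .6 as a standardized mean difference, one could report a fall from 41 % to 35 % at ICC .05, and to about 20 % on 6 df. That reading does not reproduce the stated 97 %. It mixes a separate question about the effect-size metric with the cost of clustering.

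**F-COPES.** The scale "will be administered to both dyad members", and one might infer that the two scores will be pooled as if independent. The article nowhere specifies a pooled analysis, so this is at most a condition to note.

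**The remedy is fragile.** With 4 to 5 cohorts per arm, the variance estimate is often zero, and a fit that drops the term returns to the criticized model. This stands and shapes the fix.

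**It might be left to the analysis plan.** This does not stand. The article itself sets out the fixed factors, the random effects and the dependence to be handled. Its covariate clause concerns prognostic factors found imbalanced at baseline, not treatment groups formed afterwards.

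**Conclusion.** The stated model does not match the stated delivery: treatment is given to cohorts, while the mixed model, the repeated-measures ANOVA and the power calculation all treat dyads as independent. That mismatch is certain from the text; its size is not.

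Under an assumed ICC of .05 to .10 and four cohorts of 4 per arm, the true error rate is about 1.3 to 2.4 times the nominal .01. At ICC .20 it is about 2.4 to 4.2 times, and at .01 essentially nominal. Whenever the ICC is positive, the error runs toward false superiority.

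The 97 % power is overstated for any analysis with cohort as the unit of inference. Even at ICC 0 it becomes 84 % or 91 %, from the degrees of freedom alone. The power figures rest on .6 being Cohen's f and on the same ICC in both arms.

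**What to change.** - **Model.** Add a random effect for treatment cohort, nested in arm, to each mixed model. Use one pooled variance unless a separate one per arm can be estimated. Add cohort-by-time where estimable, because group delivery cannot affect pre-treatment scores and the group-by-time test depends on what happens afterwards.
- **Degrees of freedom.** Fix in advance that group tests use between-cohort degrees of freedom (6 with four cohorts per arm, 8 with five), including when the cohort variance is estimated at zero. Name a cohort-level analysis as the fallback.
- **Repeated-measures ANOVA.** State that this sensitivity analysis ignores clustering, or run it on cohort summaries.
- **Power section.** Say that the 97 % ignores clustering, say what the effect size of .6 measures, and give power over a stated ICC range, for example 77 % to 87 % at .05 and 71 % to 83 % at .10.
- **F-COPES.** If both members' scores are ever modelled together, add a random effect for dyad.

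The cost is wider intervals and lower stated power, even if the true ICC turns out to be near zero. Enrolment and data collection do not change, provided cohort membership is recorded for every dyad.
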